## Abstract

**Background:**

SARS-CoV-2 infection rapidly spreads in populations due to the high rates of community transmission. Interrupting the shedding of SARS-CoV-2 may reduce the incidence of Coronavirus Disease 19 (COVID-19). Herein we provide a protocol for a cluster randomized trial that will examine the effectiveness of treatment with interferon (IFN) ß-1a compared to standard of care in limiting the transmission of SARS-CoV-2. Co-primary objectives are to determine whether IFN therapy reduces (a) the proportion of infected cases shedding SARS-CoV-2 at day 11 post randomization and (b) the incidence of transmission of SARS-CoV-2 infection from index cases to treatment-eligible household post-exposure contacts at day 11 after randomization. Secondary objectives include assessing the impact of IFN treatment on duration of viral clearance, hospitalizations and fatalities, and evaluating the safety of IFN treatment.

**Methods:**

Three hundred and ten households, each including an index case with a recent COVID-19 diagnosis and at least one asymptomatic treatment-eligible household contact, will be randomized to receive 3 doses of 125 μg IFN ß-1a by subcutaneous administration (days 1, 6, and 11), or standard of care. All participants will be followed until day 29.

**Discussion:**

The results from this trial will identify whether IFN ß treatment of mild or moderate COVID-19 cases accelerates viral clearance and prevents disease progression and whether IFN ß treatment of post-exposure contacts of COVID-19 cases reduces transmission of infection.

*Trial Registration:* This trial is registered at ClinicalTrials.gov NCT04552379; date of registration September 17, 2020.

## Background

Since the emergence of coronavirus disease 19 (COVID-19) in China in December 2019, there have been over 190 million cases worldwide and more than 4 million deaths to date [1]. Following the Severe Acute Respiratory Syndrome (SARS) in 2002 [2] and Middle East Respiratory Syndrome (MERS) in 2012 [3], SARS-CoV-2 has emerged as the most serious human coronavirus infection in 20 years. In approximately 80% of cases, SARS-CoV-2 infection results in mild to moderate COVID-19, with symptoms similar to common respiratory diseases such as influenza-like illnesses [3]. In 14% of cases, SARS-CoV-2 infection results in severe disease requiring oxygen supplementation and/or mechanical ventilation, with a further 2–75% progressing to respiratory failure, septic shock and/or organ failure [4, 5].

Even with the recent availability of vaccines, global herd-immunity remains elusive. Worldwide efforts to reduce SARS-CoV-2 infection rates continue, with preventative measures including distancing, use of facemasks in public places, and hand hygiene measures. Many countries have also implemented mandatory quarantine and contact tracing [6]. Individuals infected with SARS-CoV-2 shed virus and may be contagious for up to 5 days prior to developing symptoms (‘pre-symptomatic transmission’) [7–9]. Notably, nearly 60% of all infected subjects can shed virus pre-symptomatically [10]. Pre- or even asymptomatic shedding occurs across all age groups, even in children [11], and has contributed to the rapid expansion of the pandemic [7, 10]. Since pre-symptomatic shedding of virus can start up to 5 days prior to symptom onset, any post-exposure prophylaxis intervention for contacts recently exposed to a case could interrupt the spread of the virus.

With this strategy in mind, we have focused on the potential of post-exposure prophylaxis with interferon (IFN). Type I IFNs, IFN-αs/ß, are associated with the earliest innate immune response to viral infections. Type I IFNs invoke direct antiviral effects against different stages of viral replicative cycles and also activate immune cells to mediate viral clearance [10]. Certainly, the scientific literature is replete with evidence that pre-treatment of cells or small animals with an IFN-α or an IFN-β can protect from subsequent viral challenge. Type I IFNs were approved for therapeutic use in the context of chronic hepatitis C virus infection, in the 1990s. Notably, type I IFNs have seen limited clinical use for acute virus infections.

A clinical study that evaluated the therapeutic potential of a type I IFN against SARS, demonstrated rapid resolution of lung abnormalities in hospitalized cases treated with IFN-α [12]. More recently, results from an exploratory study undertaken in Wuhan, China, at the start of the SARS-CoV-2 pandemic, provided evidence that IFN treatment of moderate COVID-19 cases led to diminished lung pathology and accelerated viral clearance from the airways [13, 14]. Viewed altogether, the data suggest that IFN treatment for acute respiratory coronavirus infections may offer therapeutic benefits. Given the high SARS-CoV-2 transmission rates, especially with the emerging variants of concern, and the uncertainty surrounding achieving global herd immunity with vaccines, the major objective of this trial is to examine the safety and efficacy of post-exposure prophylaxis with IFN ß-1a in close contacts of confirmed COVID-19 cases. Herein we report the protocol of the Containing Coronavirus Disease 19 (ConCorD-19) study.

## Methods/Design

### Study overview

ConCord-19 is a prospective, cluster randomized trial of pegylated IFN ß-1a (PLEGRIDY®) treatment versus standard of care for index cases positive for SARS-CoV-2 infection and their household contacts. Index cases will be identified from acute respiratory COVID-19 clinics, primary care clinics and hospitals, reporting evidence of SARS-CoV-2 infection by RT- PCR. Household contacts will be identified via the index cases and will be approached to participate following consent from the index case.

Households will be randomized to receive IFN ß-1a or clinical care recommended by the Ministry of Health or the patient´s medical provider. Study participants will continue to follow national guidelines regarding self-isolation and infection prevention during study participation. The study design is described in Fig. 1.

**Fig. 1 Fig1:**
[figure not shown]
Diagram of ConCorD-19 study

### Primary and secondary objectives

The two co-primary objectives of this study are:To determine whether IFN ß-1a treatment reduces the proportion of infected cases shedding SARS-CoV-2 at day 11 after randomization.To determine whether IFN ß-1a treatment reduces the incidence of SARS-CoV-2 transmission from index cases to treatment-eligible household contacts, as measured by any positive upper airway infection evidenced by real-time Polymerase Chain Reaction (RT-PCR), in contacts at day 11 after randomization.

Secondary objectives of this study are:To determine whether in index cases infected with SARS-CoV-2, IFN ß-1a treatment compared with standard of care reduces the duration of SARS-CoV-2 upper airway virus shedding over 28 days following randomization.To determine whether IFN ß-1a treatment affects the incidence of SARS-CoV-2 upper airway infection or serological conversion by study day 29 in household contacts.To determine whether IFN ß-1a treatment compared with standard of care reduces the proportion of infected cases that require hospital admission or die due to COVID-19.To determine the safety of IFN ß-1a in the treatment and prevention of SARS-CoV-2 infection.

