### Treatment assignment and randomization

Households will be randomized as clusters to receive either IFN ß-1a treatment or standard of care, once a household meets all the inclusion and none of the exclusion criteria. Households will be randomized to IFN ß-1a treatment or standard of care at a 1:1 ratio. The minimization technique (biased coin, *p* = 0.7) will be applied to achieve balance between groups stratified by the total number of people within the household. This will be implemented through a platform provided by the Telethon Kids Institute (https://qminim.telethonkids.org.au/).

Households will be randomized during the first home visit, once eligibility is confirmed, participants have signed informed consent, and baseline data collection procedures are completed. Field team members will contact the research laboratory, at which time the household assignment to treatment or standard of care will be made by the randomization software. Participants and study staff will not be blinded to randomization of treatment or standard of care, but all data analyses will be blinded to allocation.

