### Control arm

Participants randomized to the control group will receive standard of care, including symptom-based supportive treatment provided by the individual’s personal medical provider. This could include acetaminophen, non-steroidal anti-inflammatory drugs, cough suppressants, antibiotics, inhaled bronchodilators. Participants in this arm will not receive any IFN ß-1a treatment or a placebo. This standard of care approach was selected as the comparator, since no other approved intervention medications are available for non-hospitalized cases.

All participants, regardless of their allocation group, will receive a brochure with the recommendations of the Chilean Government for patients with COVID-19, including household isolation. Within each household, the index case will be asked to isolate from their contacts.

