### Data and safety monitoring

An independent Data and Safety Monitoring Board (DSMB) will be convened and will meet weekly for the first four weeks of the study and then monthly until database lock. The DSMB will monitor data completeness, duplication, rates of enrollment and participation, and the general study conduct. The DSMB will be composed of individuals with the appropriate expertise, including at least three independent clinicians and/or biostatisticians who, collectively, have experience in the management of biostatistics and the conduct and monitoring of randomized controlled trials. Members of the DSMB will be independent of trial conduct. The DSMB will review data from the treatment and control groups of the trial. At each meeting, a descriptive summary of withdrawals, serious adverse events and non-serious adverse events thought to be related to the study drug will be provided, along with outcome data for the primary outcomes. The DSMB will provide its input to the trial chief investigator.

Adverse events (AE) and adverse reactions (non-serious and serious) will be captured from the time of randomization until study day 29. For the purposes of this study, the investigator or delegate is responsible for recording all AE, regardless of their relationship to study treatment, with the following exceptions: (1) conditions that are pre-existing at enrollment and do not deteriorate; (2) abnormal laboratory values unless deemed clinically significant by the investigator and documented as such; (3) the onset of COVID-19 symptoms among asymptomatic household contacts or new symptoms within the household index case. The seriousness of an AE will be assessed by an investigator with the following exceptions: (1) elective surgery planned at the time of enrollment, and (2) hospitalization due to progression of disease will not be considered a serious adverse event (SAE) for the purposes of this trial.

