All adverse events/serious adverse events will have their relationship to the trial intervention and severity assessed by the investigator who evaluates the adverse event, based on temporal relationship and his/her clinical judgment. All severe adverse events will be reported immediately to the sponsor, except for those SAEs that are identified as not requiring immediate reporting. The immediate reports should be followed promptly by detailed, written reports. Clinic trial liability insurance will cover costs for participants who suffer harm during trial participation. Investigators will ensure harmed participants receive treatment for their condition.

IFN treatment is known to induce injection site erythema and, in up to 80% of recipients, an ‘influenza like’ syndrome, comprising fever, headache and body aches. Importantly, there are no respiratory signs or symptoms associated with IFN treatment, i.e. the response to IFN treatment is different than COVID-19 disease. However, ‘flu-like symptoms’ also occur in COVID-19 disease, and could lead to an increase in clinical tests in the IFN treated cohort if not appropriately managed. There are several strategies that may mitigate this potential response to IFN treatment that already constitute standard practice for multiple sclerosis (MS) patients on IFN therapy. Participants will be informed about the likely side effects of IFN treatment and asked to monitor and manage these. Monitoring consists of self-assessment of symptoms (there are no respiratory symptoms or anosmia known to be associated with IFN use) and the time frame during which this ‘influenza like’ syndrome following IFN treatment occurs (restricted to the first 4–24 h after administration of an IFN dose). Management consists of advising the participant to take acetaminnophen (provided to the participant) from the time of IFN administration up to 24 h after, to reduce the likelihood of this ‘influenza like’ syndrome. This approach is recommended for individuals with MS receiving IFN therapy (see PLEGRIDY package insert product monograph) and reduces syndrome symptoms by 80%.

Interferon ß-1a is safe when taken during pregnancy, with no evidence of increased rates of congenital anomalies or spontaneous abortions, according to data reported by the European IFNbeta Pregnancy Registry. If a female subject is diagnosed as pregnant by a positive.

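### The admission-or-death endpoint is worded by cause in an open-label trial where only one arm has a study drug to blame, and the abstract names no cause

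*Protocol article*

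**What the plan says.** Under Primary and secondary objectives, the third secondary objective is whether IFN "reduces the proportion of infected cases that require hospital admission or die due to COVID-19". The Background part of the Abstract lists the same aim as "assessing the impact of IFN treatment on duration of viral clearance, hospitalizations and fatalities", with no cause attached.

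Under Treatment assignment and randomization, "Participants and study staff will not be blinded to randomization of treatment or standard of care", although "all data analyses will be blinded to allocation". Under Control arm, "Participants in this arm will not receive any IFN ß-1a treatment or a placebo".

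Data and safety monitoring adds three relevant statements:
- For serious adverse events, "hospitalization due to progression of disease will not be considered a serious adverse event (SAE) for the purposes of this trial".
- Adverse events have their "relationship to the trial intervention and severity assessed by the investigator who evaluates the adverse event".
- Flu-like symptoms occur both after IFN and in COVID-19, and this overlap "could lead to an increase in clinical tests in the IFN treated cohort if not appropriately managed".

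Baseline and follow-up home visits says that consent will be sought for access to the records of any admission or clinic visit.

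**The concern.** Among the stated objectives this is the only clinical efficacy endpoint; the others rest on PCR, serology or safety. If an event counts only when it is attributed to COVID-19, someone has to make that attribution, and the two arms do not offer the same choices. A febrile IFN-arm participant admitted shortly after a dose could be labelled as disease or as drug reaction. The same admission in the control arm cannot be labelled as drug reaction. Blinding the analysts does not help, because the label is fixed before the data reach them.

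There is a second problem that better attribution does not solve. An admission that IFN really caused is left out of a COVID-19-specific endpoint by definition. IFN could then show fewer COVID-19 admissions while total admissions were similar or higher.

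**Working it through.** The article gives no event rate, power or sample size for this endpoint, so there is no planned figure to reproduce. The calculations below show only how far the ratio can move.

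**Inputs**
- Index cases per arm: 310 households / 2 = 155 (Sample size and power considerations).
- Control-arm risk of admission or death, p: not in the document. Assumed 3%, 5% and 10%, which gives 155 × p = 4.65, 7.75 and 15.5 control events.
- d = share of IFN-arm COVID-19 admissions labelled drug-related: assumed 10%, 20%, 30%.
- q = proportion of IFN participants with a drug-caused admission: assumed 0.5%, 1%, 2%.

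**(a) Disease read as drug, true ratio 1.** Observed RR = p(1 − d)/p = 1 − d, whatever p is. Results: 0.90, 0.80, 0.70. At p = 5% this is 7.75 control events against 7.0, 6.2 and 5.4 IFN events. The error favours IFN.

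**(b) Drug read as disease, true COVID-19 ratio 1.** Observed RR = (p + q)/p. The error goes against IFN.

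**(c) Perfect attribution, true COVID-19-specific ratio assumed 0.70.** All-cause RR = (0.70p + q)/p. The cause-specific endpoint would still report 0.70.

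| p | (b) q = 0.5 / 1 / 2% | (c) q = 0.5 / 1 / 2% |
|---|---|---|
| 3% | 1.17 / 1.33 / 1.67 | 0.87 / 1.03 / 1.37 |
| 5% | 1.10 / 1.20 / 1.40 | 0.80 / 0.90 / 1.10 |
| 10% | 1.05 / 1.10 / 1.20 | 0.75 / 0.80 / 0.90 |

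Events are few, so single labels matter. Moving one event changes the ratio by about 1/7.75 = 0.13 at p = 5%.

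**Price of an all-cause endpoint.** If unrelated admissions occur at rate u in both arms and there are no drug-caused ones, a true 0.70 becomes (0.70p + u)/(p + u). At p = 5% and u = 0.5% this is (3.5 + 0.5)/5.5 = 0.73; at u = 1% it is (3.5 + 1)/6 = 0.75. Both values of u are assumptions.

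**Population.** The third objective says infected cases and the first secondary objective says index cases. Co-primary objective 1 also says infected cases. Its analysis section uses the index cases, as does the sample-size section, and Secondary analyses carries the primary methods over to the secondary outcomes. Index cases are therefore the natural reading.

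**The case against.** A reader might infer that the comparison is biased towards IFN. The document does not support that. Its own warning, that flu-like reactions may lead to more testing in the IFN arm, describes drug effects being worked up as disease, which would count against IFN. Data and safety monitoring also exempts new symptoms in the index case from adverse event recording. That pushes such symptoms towards the disease label and narrows the route by which they become drug reactions. Error (a) and error (b) are both possible, and nothing in the article says which is larger.

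A reader might also infer that unblinded staff decide what is due to COVID-19. The article does not say who decides. The investigator's judgment it describes concerns adverse event causality, and the rule on disease progression classifies serious adverse events; neither defines the efficacy endpoint. The full protocol or analysis plan may provide for adjudication, so its absence from a condensed article is not a fault.

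Other points on that side are fair:
- The qualifier about COVID-19 may attach only to dying, and the abstract names no cause.
- The article describes IFN reactions as without respiratory signs and confined to 4 to 24 hours after a dose, so many admissions would be easy to classify.
- Drug-caused admissions are not lost to the trial. If correctly labelled, they remain in the safety data.
- All event and relabelling rates above are assumed.
- A treatment-affected denominator, with contacts infected after randomisation counted as infected cases, is not the natural reading of the text.

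These points remove the claimed direction and the denominator complaint. They leave standing the two wordings of the endpoint, the unequal choice of causes between arms, and the omission of drug-caused admissions from a cause-specific comparison. The doubt over what the qualifier covers is itself a reason to fix the wording.

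**Conclusion.** The point holds as a risk of misclassification that differs by arm, of unknown direction, on a secondary endpoint whose two descriptions do not agree. Under the assumed rates, a true ratio of 1 could appear anywhere from 0.70 to 1.67. With perfect attribution, a cause-specific 0.70 could accompany an all-cause ratio of 0.75 to 1.37. These ranges illustrate what the definition allows and do not estimate what will happen. They rest on the assumed p, d and q, and on reading the COVID-19 qualifier as covering admission as well as death. If it covers only death, the attribution problem shrinks to deaths and what remains is mainly the need for one clear definition. The two PCR co-primary endpoints do not depend on attributing a cause and are not affected.

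**What to change.** Reconcile the Abstract with Primary and secondary objectives by stating one definition: hospital admission for any reason, or death from any cause, from randomisation to day 29, in all randomised index cases. Keep events attributed to COVID-19 as a supportive analysis, preferably classified by people who do not know the allocation.

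No new data are needed, because record access is already sought for any hospitalization. The all-cause definition removes both labelling errors and brings drug-caused admissions back into the comparison. It does not remove any influence of known allocation on the decision to admit.

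The costs are small. Unrelated admissions dilute the effect slightly (0.70 to about 0.73–0.75 in the example above). Since 251 of 310 households were already enrolled at submission, the change is a modification of a running trial and must be reported as the Protocol modifications section requires. It should be agreed without sight of this outcome by arm.

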### Setting

The study will take place in the Santiago metropolitan area in Chile, population 7,112,808 [15]. Chile’s healthcare system has private and public providers, and insurance systems. Country-wide, Chileans have access to good primary health care and hospital networks, achieving a life expectancy that places Chileans in the global upper quintile [16]. In Chile, the first case of COVID-19 was confirmed on March 3, 2020, [17] with 608,973 confirmed cases and 16,608 confirmed deaths in 2020 [18].

### Study population and inclusion/exclusion criteria

The study population will include individuals, between the ages 18 and < 80 years, who have tested positive for SARS-CoV-2 (RT-PCR) within the previous 72 h (Index Cases) and their household contacts (Eligible Contacts, between ages 18 and < 80 years, and Ineligible Contacts). Eligible households must include at least one eligible index case and one eligible household contact. Treatment ineligible participants will also be enrolled, to assess SARS-CoV-2 transmission within a household. Details of household and participant eligibility are proved in Fig. 2 and Table 1.

**Fig. 2 Fig2:**
[figure not shown]
Household and participant eligibility

**Table 1 Tab1:** Participant inclusion and exclusion criteria

	Inclusion criteria	Exclusion criteria*
Index cases	• Provided a signed and dated informed consent form • Aged 18 to < 80 years of age • Confirmed SARS-CoV-2 diagnosis by PCR within 72 h of first treatment dose • The first known diagnosis in the household • Not currently enrolled in a clinical trial and agree to not take any other investigational treatments over the next 28 days • Must plan to remain resident in the household during the study • Lives in household with at least one other ‘treatment-eligible household contact	• Inability to take medications orally or by injection • Known sensitivity/allergy to interferons or use of interferons for another indication • Known adverse drug-drug interactions with any study drugs • Malignancy • Known clinical immune deficiency • Pregnancy or unwillingness of female participant of childbearing age to use recognized methods of birth control/contraception during the trial period • Retinopathy • Known grade 4 or 5 chronic kidney or liver disease • Known arrhythmias • Known autoimmune disease or chronic inflammatory disease • Chronic liver disease • Hospitalization for depression in the last 3 months • Current suicidal ideation • Previous therapeutic use of IFN
Treatment eligible contact	• Provided a signed and dated informed consent form • Aged 18 to < 80 years of age • Not currently enrolled in a clinical trial and agree to not take any other investigational treatments over the next 28 days • Must plan to remain resident in the household during the study • No history of previously confirmed SARS-CoV-2 diagnosis	
Treatment ineligible contact	• Provided a signed and dated informed consent form, parental informed consent, and assent if applicable • Under 18 years OR ≥ 80 years of age OR aged 18 to < 80 years with any contraindication for IFN treatment listed in ‘exclusion criteria’ • Not currently enrolled in a clinical trial and agree to not take any other investigational treatments over the next 28 days • Must plan to remain resident in the household during the study • No history of previously confirmed SARS-CoV-2 diagnosis	

^*^All household members are ineligible if participation by any member is declined or if the index case has been in complete self-quarantine from other household members during the 48 h prior to diagnosis of SARS-CoV-2 infection

